#### Baseline interview

All the participated patients will be required to complete a survey either via an online survey through their mobile phone or via a printed brochure. The contents of the survey contain three parts, including patients’ clinical parameters (warfarin indication, start date of warfarin, warfarin dosage, previous TTR, history of thrombosis or major bleeding, concomitant diseases and medicine), behaviour indicators (warfarin knowledge, anticoagulant compliance, treatment behavior and quality of life) and costs on warfarin related treatment.

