#### Follow-up visits and data collection

Each of the enrolled patients has to record his/her warfarin related information in a printed monitoring handbook, including INR results, warfarin dosage, other medicine, diet change, new disease, and thrombosis or bleeding events (if occurs). All the patients are required to receive follow-ups at the 3rd, 6th, 9th and 12th month through outpatient clinic visits, telephone or online interviews. At each follow-up time-point, the research stuff will collect the warfarin related information. Double data entry will be carried out to ensure data accuracy and data will be kept in encrypted mobile hard disks to protect patients’ privacy. Only the corresponding author has access to the final trial dataset. As shown in Table 3, patients are required to provide the information of warfarin dosage and INR results, the numbers of going to the outpatient clinics or inpatient treatment due to warfarin, quality of life as measured by the health index scale (EQ-5D-3L) [16], and the related treatment costs. At baseline and the last time visit, patients are required to fill in the Morisky anticoagulant compliance questionnaire [14] and the oral anticoagulation knowledge test [15]. An anticoagulation satisfaction survey by using the Duke Anticoagulation Satisfaction Scale [17] will be conducted to all the patients at the end of the study. The research staff will send text messages to remind the patients for follow-ups and all the participated patients will receive certain amount of compensation fees to sustain their involvement in the study.

**Table 3 Tab3:** Measurement domains, survey methods and collection time-points

Variable	Component	Measurement methods	Baseline	3rd M	6th M	9th M	12th M
**Socio-demographic parameters**	Gender, age, telephone, address, education, occupation and annual income	Face-to-face interview	√				
**Clinical parameters**	Height, weight, warfarin indication, start date of warfarin, warfarin dosage, TTR calculated by INR tests in the preceding 12 months, history of thrombosis or major bleeding, concomitant diseases and medicine Warfarin dosage, INR, bleeding or thrombosis, other clinical adverse events	Face-to-face interview	√				
		Face-to-face interview, telephone or online interview		√	√	√	√
**Behaviour parameters**	Anticoagulant compliance, warfarin knowledge,	Morisky Anticoagulant Compliance Questionnaire [14], Oral Anticoagulation Knowledge (OAK) Test [15]	√				√

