	Treatment behavior, quality of life	Self-made questionnaire, EQ-5D-3L Form [16]	√	√	√	√	√
	Anticoagulation satisfaction	Duke Anticoagulation Satisfaction Scale [17]					√
**Economic parameters**	Direct costs (INR test fees, outpatient clinic visit fees, hospitalization or emergency room visit fees if occurs), Indirect costs (deducted income due to absence of working, traffic and accommodation fees)	Face-to-face interview, telephone or online interview	√	√	√	√	√

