#### Secondary outcome measures

The numbers of INR results indicating excessive under-coagulation or over-anticoagulation (INR < 1.5 or INR > 5.0).Serious adverse clinical events (clinical relevant non-major bleeding, major bleeding, thrombosis or death)Patients’ quality of life.Costs on warfarin management.

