#### Data analyses

We will report continuous variables as means ± SD and categorical variables as proportions. Data will be checked for normal distribution by means of the Kolmogorov–Smirnov’s test. In compliance with the distribution of data, Student’s t-test or Mann–Whitney’s U-test will be used for comparisons between the SMART model group and control group. Chi-square or Fisher’s exact tests will be used to compare between the SMART model group and control group with respect to categorical data. The control of anticoagulation will be assessed by evaluating TTR with the Rosendaal method [18] in each arm. The follow-up assessment data will be analyzed using Generalized Linear Mixed Model and survival analysis. *P* ≤ 0.05 is considered statistically significant. All tests are two tailed. From the perspective of health-care payer, we will conduct a cost-effectiveness analysis to assess the economic impact of the SMART model for warfarin home management. A Markov model, a half-cycle correction and a discount of 5% will be constructed or used to estimate the total costs and quality-adjusted life-years (QALYs) over the 2-year period (the outcomes beyond the observation period will be predicted according to the results obtained in the study). We will collect the direct and indirect costs of each enrolled patient on warfarin, evaluate their quality of life through EQ-5D-3L utility value from data provided by patients, calculate QALYs, and analyze the effects of multiple variables by the Linear Mixed Effects Model. The direct costs include laboratory INR test fees in the control groups (or POCT fees in the SMART model group), outpatient clinic visit fees (or supervision fees in the SMART model group), hospitalization fees and emergency room visit fees. The indirect costs include deducted income due to absence of working, traffic fees and accommodation fees. Because warfarin is very cheap, the medication fee of warfarin is not calculated in each group. The incremental cost effectiveness ratio (ICER) will be calculated according to the total costs and QALYs, and one-way and probabilistic analyses will be performed to verify the stability of the model.

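### Baseline EQ-5D-3L utility and costs are collected, but the Data analyses section does not say which analysis gives the quality-of-life contrast, nor tie that contrast or the ICER inputs to the baseline values

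*Protocol article*

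**What the plan says.** **Data collected.** The baseline interview covers "behaviour indicators (warfarin knowledge, anticoagulant compliance, treatment behavior and quality of life) and costs on warfarin related treatment". Under Follow-up visits and data collection, patients report "quality of life as measured by the health index scale (EQ-5D-3L) [16], and the related treatment costs". Table 3 schedules the EQ-5D-3L and both direct and indirect costs at baseline and at months 3, 6, 9 and 12.

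**Status of the outcomes.** Both are listed as secondary outcomes: "Patients’ quality of life.Costs on warfarin management".

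**Analysis.** The Data analyses section contains four statements that bear on them:

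- For continuous data, depending on distribution, "Student’s t-test or Mann–Whitney’s U-test will be used for comparisons between the SMART model group and control group". No outcome is named.
- "The follow-up assessment data will be analyzed using Generalized Linear Mixed Model and survival analysis". No covariates are listed.
- In the sentence on costs, EQ-5D-3L utility and QALYs, a linear mixed effects model is to examine the effects of multiple variables, which are not listed.
- Total costs and QALYs are estimated with a Markov model over 2 years, with half-cycle correction and 5% discounting. Then "The incremental cost effectiveness ratio (ICER) will be calculated according to the total costs and QALYs", with one-way and probabilistic analyses.

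Baseline utility and baseline cost are not named as covariates in any of these statements.

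**The concern.** Two kinds of analysis are named for the same quality-of-life data, a two-sample test and a mixed model, and nothing says which provides the reported contrast. If the two-sample test does, the baseline measurement goes unused. The same gap affects the economic analysis: nothing says whether the trial utilities and costs that feed the Markov model and the ICER are adjusted for baseline.

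This matters because utility usually correlates with itself over time. If one arm starts higher by chance, it will tend to stay higher, and an unadjusted comparison counts that head start in the arm difference. The incremental QALY is the denominator of the ICER, so when it is small a modest shift can change the ratio a good deal. The Discussion makes wider use of the model conditional on showing cost-effectiveness, and outcomes beyond the observation period are to be predicted from the trial results. The primary outcome, TTR, is not affected.

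**Working it through.** **No plan figure to reproduce.** The article states no SD, correlation, effect size or power for utility, costs, QALYs or the ICER. Its only sample-size figure (31 per group) is for TTR and does not bear on this point. What follows is an illustration under assumptions.

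**Inputs from the document.** Visits at months 0, 3, 6, 9 and 12 (Table 3). Arm sizes are 360 SMART and 360 usual care. The anticoagulation clinic arm has 120, with 120 SMART patients at the same hospital level (Randomization).

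**Assumed.** A 12-month area-under-the-curve QALY; utility SD of 0.20 at every visit (range 0.15 to 0.25); equal correlation ρ between any two visits, 0.3 to 0.7.

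**Step 1: weights.** The trapezoid rule gives 1/8, 1/4, 1/4, 1/4, 1/8. The sum of squares is 2 × 1/64 + 3 × 1/16 = 0.21875.

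**Step 2: variance, slope and R² (per unit SD).**

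- Var(QALY) = 0.21875 + 0.78125ρ
- Slope of QALY on baseline utility = 0.125 + 0.875ρ
- R² = slope² / Var(QALY)
- Fall in standard error from adjustment = 1 − √(1 − R²)

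| ρ | Var | Slope | R² | Fall in SE |
|---|---|---|---|---|
| 0.3 | 0.453 | 0.388 | 0.331 | 18% |
| 0.5 | 0.609 | 0.5625 | 0.519 | 31% |
| 0.7 | 0.766 | 0.738 | 0.710 | 46% |

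The slope is the share of a baseline utility difference that passes into the unadjusted QALY difference: 39% to 74%. The percentage fall in SE does not depend on the assumed SD or on the arm sizes.

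**Step 3: absolute size at SD 0.20 and ρ = 0.5.**

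- SE of the baseline difference = 0.20 × √(2/n): 0.0149 for n = 360 and 0.0258 for n = 120.
- Shift in incremental QALYs from a one-SE chance imbalance = 0.5625 × SE: 0.0084 and 0.0145.
- SE of incremental QALYs = 0.20 × √0.609 × √(2/n): 0.0116 unadjusted against 0.0081 adjusted for n = 360, and 0.0202 against 0.0140 for n = 120.

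**Step 4: range.** Over SD 0.15 to 0.25 and ρ 0.3 to 0.7, a one-SE imbalance shifts incremental QALYs by 0.004 to 0.014 (360 v 360) or 0.008 to 0.024 (120 v 120).

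**Limits.** These figures describe a patient-level 12-month QALY. The planned ICER uses 2-year Markov totals, and the article does not describe how trial utilities and costs enter the model states, so the pass-through to the ICER cannot be computed. No calculation is offered for costs, for which the documents give neither a spread nor a correlation.

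**The case against.** The strongest reply is that the article does not commit to an unadjusted analysis. The two-sample tests are a general statement for continuous data. EQ-5D-3L and costs at months 3 to 12 are follow-up assessment data, for which a mixed model is planned, and a second mixed model appears in the very sentence on costs, utility and QALYs. Either could include baseline, and a covariate list is something an article commonly leaves to the full plan.

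Much of this stands. A reader might infer that quality of life will definitely be compared by t-test and that the ICER will be built from raw arm totals. The text does not support that: it ties the two-sample tests to no outcome and does not call the totals raw or unadjusted. The missing covariate list alone would not be a finding either. What remains is that the article names competing methods without ranking them, that the only test it names explicitly for comparing the arms on continuous data cannot use baseline, and that neither mixed model is said to provide the quality-of-life contrast or the ICER inputs.

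It is also fair to say that, with randomised allocation, imbalance is a matter of chance and a valid unadjusted standard error already reflects it. A reader might infer bias in favour of SMART; the argument here does not show that. Carried-over imbalance and lost precision are two views of the same sampling variability and should not be counted twice. The one-way and probabilistic analyses do not settle the matter, since they vary the model inputs without adjusting them for baseline.

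**Conclusion.** The concern holds as one of unclear specification and avoidable imprecision in the secondary and economic outcomes. Followed as written, the plan permits a less precise analysis than its own data support. For a 12-month area-under-the-curve QALY the cost is an SE that baseline adjustment would lower by about 18% (ρ = 0.3), 31% (ρ = 0.5) or 46% (ρ = 0.7), assuming equal SDs and equal correlations across visits. Those correlations are assumptions and do not come from the documents.

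The percentages should not be read as the error in the planned ICER. They apply to a different estimator, and the effect on the Markov output depends on inputs that the article does not describe. Nor is any effect on TTR implied.

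**What to change.** In the Data analyses section, state that:

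1. EQ-5D-3L utility over months 3 to 12 is compared between arms with the mixed model already planned, with baseline utility and hospital level as covariates, in place of the t-test or Mann-Whitney test. Hospital level belongs there because enrolment is set per arm within each level and the anticoagulation clinic arm exists only at the high level.
2. The trial-based utility or QALY differences and the cost differences that feed the Markov model and the ICER are adjusted for baseline utility and baseline cost respectively.
3. The unadjusted result is reported as a sensitivity analysis.

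If a fuller plan already says this, a sentence confirming it is enough. The change is analysis wording only: the variables are already scheduled for collection and the model class is already planned. The small downside is that a missing baseline EQ-5D or cost value needs simple imputation.

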### Sample size determination

In order to detect a hypothetical TTR difference of 5% between the SMART model group and the control group with a power of 80% and a significance of *P* = 0.05, a sample size of 31 patients in each group is required [19]. An additional 10% is added to allow for patients dropping out of the study, thus a sample size of at least 34 patients in each arm is needed.

### Dissemination

The research results will be disseminated through publications in peer-reviewed journals, academic conferences seminars and workshops. Articles and videos related to warfarin management made in plain words will be shared to public in website for free.

## Discussion

In a recent review, scientists believe SARS-CoV-2, the virus caused the Coronavirus Disease 2019 (COVID-19) pandemic, will continue to evolve and evade human immunity. They have predicted three scenarios, and the most likely scenario is that the COVID-19 pandemic will develop to an epidemic seasonal disease like influenza [20], which will influence human health for a long time. During the pandemic, many patients have delayed or avoided hospital visits due to fear of getting infected. This phenomenon is particularly obvious among the elderly patients or patients living in rural areas. Complying with the social distancing regulations, many countries are encouraging hospitals to conduct telehealth visits and other interactions with patients. As a result, the use of telehealth has been significantly increased in many countries, including China. Therefore, we believe COVID-19 will last for a long time and the telehealth will be widely accepted and applied in the healthcare system across the world.

While not new, warfarin home management via telehealth and a POCT device for INR measurement has received widespread acclaim in developed countries. There are mainly two patterns of warfarin home management. One pattern is patient self-testing, of which patients perform INR tests followed by the adjustment of warfarin dosage guided by a healthcare provider. The other pattern is patient self-management, of which patients perform INR tests and adjust warfarin dosage by themselves. Patients’ frequent home monitoring enables the abnormal INR values to be identified in time, attributing to lower risks of adverse events. A meta-analysis showed 50% reduction in the incidence of thromboembolic events in the warfarin home management group compared with the usual care group [10]. Warfarin home management has been proved as safe as traditional care in terms of major bleeding events [21]. The patients who received home management showed improved satisfaction and better quality of life compared to the usual care group [22]. Furthermore, warfarin home management is cost-effective [23]. As a result, coverage under Medicare was approved in 2002 for the indication of mechanical heart valves and in 2008 for other diseases including atrial fibrillation in the United States.

Nevertheless, the implementation of warfarin home management faces obstacles in developing countries, including legal and regulatory issues, patients lacking direct and timely access to professional recommendations from health care providers, lack of access to telehealth technology, and limited or no coverage of the POCT device from the government. The current proposed study will take several measurements (the SMART model) to ensure its implementation in China, including using a mobile phone app to assist caregivers managing warfarin more efficiently, establishing medical alliance and multidisciplinary teams to manage patients together to solve the problem of maldistribution of medical care, and using a hierarchical strategy to manage patients to assure their safety. As far as we know, this proposed study will be the biggest multi-center randomized controlled trial to investigate the safety, effectiveness and cost-effectiveness of warfarin home management in China. If our final data demonstrate the SMART model for warfarin home management is cost-effective, this pattern may be applied in more provinces and be expanded to other chronic diseases management.

In the proposed study, we will include hospitals with different qualities of medical service. On the one hand, as the current medical service level in the county hospitals is low, we expect that the differences in TTR, numbers of under-coagulation or over-anticoagulation, and serious adverse clinical events between the SMART model group and the control group may be significantly bigger than the other two levels of hospitals. On the other hand, patients’ quality of life and costs on warfarin management may be improved the most obviously in the big tertiary hospitals, as patients do not have to travel long way to the hospitals.

The biggest limitation of our proposed study is that the nature of the intervention method (the SMART model) excludes patients who are unable to use a POCT device correctly, or fail to report their INR results through a mobile phone based app.

In summary, we have developed a novel model (the SMART model) to investigate the safety, effectiveness and cost-effectiveness of warfarin home management in different areas of Hunan province in China. This model may be particularly useful to manage patients on warfarin during and after the COVID-19 pandemic.

### Trial status

Recruitment has begun in March 2021.

## Data Availability

The datasets generated and/or analyzed during the current study are not publicly available but are available from the corresponding author on reasonable request.

## Abbreviations

SMART: Safe Multidisciplinary App-assisted Remote patient-self-Testing
INR: International normalized ratio
TTR: Time in therapeutic range
AC: Anticoagulation clinic
POCT: Point-of-care testing
PST: Patient self-testing
UC: Usual care clinic
XY: Xiangya hospital
QALYs: Quality-adjusted life-years
ICER: Incremental cost effectiveness ratio
COVID-19: Coronavirus Disease 2019
